## **Duration of the Study and Participant Involvement**

### **Study Duration and Schedule of Events:**

The trial is expected to start in spring 2018 (May – June 2018), and enrolment will end in the late summer of 2020. After about two months from the end of recruitment, all data will be collected. Data analysis will be performed by a PhD student supervised by CI.

### **Participant Duration:**

Six- Eight weeks including any induction period.

### **End of the Trial**

The end of the trial will be on the last participant visit.

## **Selection and Withdrawal of Participants**

### **Recruitment**

A selection of eligible people for the study will be invited from existing databases held at Academic Rheumatology of participants with knee pain who have agreed to be contacted for future studies. Any shortfall in the recruitment will be compensated by sending study leaflet to GP surgeries. Potentially eligible people are all men and women, aged between 45 years and older, registered with the GP surgery. The screening of existing records can be done by members of their direct healthcare team for those who had x-rays and osteoarthritis of the knee had been established. The GPs will exclude anyone with a known terminal illness, severe psychiatric illness or dementia, or with any other condition or circumstance that makes them unsuitable for the study. All those individuals who are suitable for the study will be sent the study information sheet so they can have some time to think about the research and what is involved in this study.

The study team in Academic Rheumatology will invite interested participants to start the study and this will be considered as the first session. The purpose of the visit will be to establish suitability by proceeding with radiographs for those who have not had x-rays in last 12 months. Those who had x-rays in previous 12 months and qualified for this study will be an exception from x-rays, and they would proceed with the assessment after signing the consent form. The research team will seek consent from the individuals who have not had X- rays, and they will go through the x-rays of a painful knee. If their x-rays demonstrate radiographic evidence of osteoarthritis (K/L= 1 or above), will be included in the study. Those individuals, where their K/L score <1, will be considered as screening failure and will be excluded from the study. All qualifying individuals will be randomised to interventional and control group.

Participants will be free to leave the study at any time without giving any reason. Participants who indicate in their questionnaire that they are willing to receive information about future OA studies may withdraw this indication at any time, and this will be altered appropriately on the

study database. Participants will be made aware via the questionnaire that all data will remain confidential and will be anonymised before use in further analysis.

It will be explained to the potential participant that entry into the trial is entirely voluntary and that their treatment and care will not be affected by their decision. It will also be explained that they can withdraw at any time, but attempts will be made to avoid this occurrence. In the event of their withdrawal, it will be explained that their data collected so far cannot be erased, and we will seek consent to use the data in the final analyses where appropriate (via the information sheet and consent form). Those who withdraw from the study will be made aware that this will not in any way affect their future care.

**Inclusion criteria:** Aged 45 years and onward.

Clinical diagnosis of knee arthritis with complaints of knee pain for 3 or more months, early morning stiffness <30 minutes, crepitus, bony tenderness, and no palpable warmth and radiographically established osteoarthritis (at least score 1 on K/L scale)

Able to read and write English

Able to use/access computer or tablet and have access to internet

**Exclusion criteria:** Inability to give informed consent – (capacity levels are already established under GP care)

Terminal or mental illness

Neurological conditions, inflammatory joint diseases including rheumatoid arthritis, gout or calcium pyrophosphate deposition disease (CPPD), and dementia

Participants with sleep apnea

Acute soft tissue injury to the knee within last 3 months before recruiting

Unstable heart condition or rapid fluctuations in hypertension

BMI>50

## **Informed consent**

All participants will provide written informed consent. The Informed Consent Form will be signed and dated by the participant before they enter the trial. The Investigator will explain the details of the trial and provide a Participant Information Sheet, ensuring that the participant has sufficient time to consider participating or not. The Investigator will answer any questions that the participant has concerning study participation.

Informed consent will be collected from each participant before they undergo any interventions (including physical examination and history taking) related to the study. One copy of this will be kept by the participant, one will be kept by the Investigator, and a third will be retained in the participant's hospital records.

Should there be any subsequent amendment to the final protocol, which might affect a participant's participation in the study at any part, continuing consent will be obtained using an amended Consent form which will be signed by the participant.

## **Future contact**

Participants will be asked to indicate on the questionnaire whether they are willing for their contact details to be stored on a secure database in Academic Rheumatology, to enable them to be informed of future studies relating to knee pain and OA undertaken by Academic Rheumatology and the Pain Centre for which they might be suitable. Participant data will be kept up-to-date in accordance with Data Protection Act, 1998. The consent form includes an

optional clause asking participants to confirm whether they are happy for their personal details to be retained for this purpose - if not their contact details will be destroyed at the end of this study after it is no longer necessary to contact them.

## **Study Regimen**

Participants seeking care for osteoarthritis will be informed of the study both orally and in writing. Those who qualify for the study will sign the informed consent and the participants will be randomised to interventional group and control group. The exception applies to those Participants who have not had knee X-rays in last 12 months. These individuals will be called to the hospital. After gaining a valid consent, knee radiographs will be taken, and their X-rays will be verified by experienced staff. Once, a definite eligibility criterion (K/L score at least 1 or above) is established in such cases, the potential participants will be randomised to interventional group and control group like the other individuals. Blinding such interventional studies are difficult to achieve as participants will establish as to in which group they are in however study will be blinded to the examining clinician. Controlled and interventional groups individuals will be recruited for this study. Interventional groups will have an assessment session with the experienced staff and NRS, QST, WOMAC, MSK-HQ, 30CST, TUG, PSQI, MSK-USS, urine and blood samples will be taken at baseline.

Interventional group will shortly after that receive a link via email, which will be used to log-in to Joint Academy online portal. After log-in has been achieved, the intervention starts. It consist of a 6-week internet-based physical therapy program that provides information, exercises, contact details of a personal physiotherapist, education about lifestyle and behavioural changes. This intervention can be accessed using a smartphone, a tablet or a computer. The program encourages the physical activity by sending email prompts on a regular basis to help participants to continue during the whole treatment. Initially, participants will answer an online-questionnaire covering areas such as joint pain intensity, health-related quality of life, physical function as well as being instructed in and performing a physical test assessing lower limb strength / physical function. This questionnaire will form a part of online baseline assessment. Exercises itself consistent of knee and hip exercises along with some functional activities such as sit to stand and stairs climbing. Interventional group will be given actigraphy device (a device to monitor sleeping pattern) which is CE marked. Therefore, their sleeping pattern can be recorded quantitatively.

Once exercises programme is finished in six weeks, the participants will fill in the same questionnaire and perform the physical tests, to enable evaluation. There are two face-to-face meetings between participants and physiotherapist/nurse, at enrolment and after six weeks. The physiotherapist is also available via asynchronous online chat or over the phone during the 6-week study period. After six weeks, participants can continue with sustain-program for self-management, mainly focusing on the continuation of treatment, performing the exercises regularly.

Control group will continue with their routine self-management which is offered in the community setup. They will be assessed on NRS, QST, WOMAC, MSK-HQ, PSQI, 30CST, TUG, isokinetic muscles strengthen of quadriceps, urine and blood samples at baseline. Control group will also get the actigraphy to monitor sleeping pattern of that group. They will be re-assessed after six weeks on the primary objective measures to see if they have made any difference by following self-management strategies in the community.

The suggested study utilises a pragmatic approach, where all participants with clinical knee OA that would have been eligible for a face-to-face program are included if they can handle a computer, tablet or smartphone.

To summarise, the total study duration, including recruitment and the two assessment visits, will be 12-15 months. The key stages are detailed below;

- Individuals who agree to attend for a clinical assessment will participate for two appointments. This appointment will last approximately 2-3 hours.
- They will be seen at the Academic Rheumatology Unit, Clinical Sciences Building, Nottingham City Hospital and will be asked to come between 8.00am and 10.00am without having had breakfast or any drink other than water.
- Transport (taxi) will be arranged if required and any travel expense will be reimbursed.
- Our Research Nurses will get a 15ml blood sample from the participant and also ask the participant to provide a urine sample.
- Once blood and urine samples have been collected participants will be offered a light breakfast and drink refreshment before a brief assessment to confirm medical history and current medications. Questionnaires such as WOMAC, MSK-HQ and Numeric Rating Scale will be collected.
- Physiological measurements such as 30 seconds sit to stand (30CST), time up and go (TUG) and Muscle strength assessment will be taken at this point.
- Quantitative sensory testing to test the sensitivity to mechanical pressure and pain.
- Participants will be asked if they wish to donate a faecal sample and if they agree they will be given a collection kit to take home, which will be shipped back by post.
- Participants will be shown how to wear actigraphy device and will be familiarised with the equipment. Each participant will take one device with them, therefore, their sleeping pattern can be assessed.
- Participant will be expected to login to online exercises portal on daily basis and complete the exercises which consist of 30 minutes of exercises and some educational videos.

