### **PRIMARY OBJECTIVE**

1. Carry out an exercise intervention in the individuals with osteoarthritis pain to assess the effect on sleep, central and peripheral pain measures

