### **Maintenance of Randomisation Codes and Procedures for Breaking Code**

As per cohort multiple randomised controlled trial design mentioned by another study (107), individuals will have an assessment to establish their suitability for this study and once, that has been established we will randomise them in to control group and interventional group. At this occasion, individuals will find out that they belong to one group or the other and hence blinding is not possible.

As the online system will be used for randomisation, therefore, code break will be kept online, and the research manager will be responsible for keeping a track if it.

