### **Randomisation**

Participants will undergo computer-generated stratified randomisation by a statistician at Academic Rheumatology using the <https://sealedenvelope.com/> software. Generation of a randomisation schedule will include obtaining the random numbers and assigning random numbers to each subject under the specific treatment conditions. Participants will be equally allocated between treatment arms with at least n=67 per arm. As the online system will be used for randomisation, therefore, code break will be kept online, and the research manager will be responsible for keeping a track of it.

As per cohort multiple randomised controlled trial design mentioned by another study (54), individuals will have an assessment to establish their suitability for this study and once that has been established, we will randomise them into control group and interventional group. At this occasion, individuals will find out that they belong to one group or the other and hence blinding is not possible. Because the lack of masking might affect the motivation of participants randomised into the control arm, individuals in the control arm will be offered access to the web-based exercise programme after the six weeks of the study, if they wish to use it to avoid a placebo effect in this group. Blinding such interventional studies are difficult to achieve as participants will establish as to in which group they are in, however, the examiner will be blinded to the intervention.

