## **Timing of outcome assessments**

All outcome variables were collected at baseline, and at follow-up (6 weeks post baseline) in both arms. However, trial was stopped on 19th March 2020 due to the COVID-19 pandemic resulting in having only 105 eligible participants completing both visits.

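### The protocol's Study Regimen puts randomisation and disclosure of arm before the baseline session, other sections can be read differently, and nothing says baseline outcomes are completed before allocation.

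*Combined protocol and SAP*

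**What the plan says.** **Order of events.** The protocol's Study Regimen says: "Those who qualify for the study will sign the informed consent and the participants will be randomised to interventional group and control group". After a remark that participants will know their group, it continues: "Interventional groups will have an assessment session with the experienced staff and NRS, QST, WOMAC, MSK-HQ, 30CST, TUG, PSQI, MSK-USS, urine and blood samples", labelled as baseline. The control arm's baseline list follows in a separate paragraph. On disclosure, Maintenance of Randomisation Codes says: "At this occasion, individuals will find out that they belong to one group or the other". The SAP's Randomisation section repeats this.

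The Recruitment section reads differently. People with a recent x-ray go on to an assessment once they have consented, and randomisation of all who qualify is mentioned last. Maintenance of Randomisation Codes and the SAP's Randomisation section also put an assessment before randomisation, but describe it as one of suitability.

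**Start of treatment.** In Study Regimen the login link goes out shortly after the clinic session, and the intervention starts at log-in. An online questionnaire covering pain, completed after log-in, is also called part of a baseline.

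**Batteries.** The intervention list includes MSK-USS but not isokinetic strength. The control list has strength but not MSK-USS. Of controls at six weeks, Study Regimen says: "They will be re-assessed after six weeks on the primary objective measures". The protocol's Primary Objective is to "assess the effect on sleep, central and peripheral pain measures", whereas the synopsis and the SAP name NRS pain as primary. The SAP's Timing of outcome assessments says: "All outcome variables were collected at baseline, and at follow-up (6 weeks post baseline) in both arms".

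**Use of baseline.** SAP Section 6 analyses change from baseline by ANCOVA on the baseline score, or by an unadjusted Mann-Whitney test of the change if the distribution is clearly non-normal.

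**The concern.** A baseline covariate or change score is safe in a randomised comparison when allocation cannot have affected it. A pain rating given by someone who has just learned that they have, or have not, been given the programme lacks that protection. The SAP itself accepts, in its Randomisation section, that lack of masking may affect motivation in the control arm.

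The measures at risk are those the participant reports or controls by effort: NRS, WOMAC, PSQI, MSK-HQ and the sensory tests (in pressure testing, for example, the participant signals the threshold). Blinding the examiner does not protect these. What is at stake is an avoidable bias in the primary estimate, of unknown size and direction.

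The unequal lists are a second, smaller matter. The SAP plans between-arm comparisons of ultrasound and strength, yet the protocol's arm-specific text does not schedule either at baseline in both arms. Its week-6 wording for controls depends on a primary objective that the documents define in two ways.

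**Working it through.** **1. Sections side by side.**

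| Section | Order it gives | Are baseline outcomes placed before allocation? |
|---|---|---|
| Protocol, Study Regimen | consent, randomisation, baseline session by arm, link, log-in | No, after |
| Protocol, Recruitment | consent, assessment or x-ray, randomisation | Possibly; the visit's stated purpose is suitability |
| Protocol, Maintenance of Randomisation Codes; SAP, Randomisation | suitability assessment, randomisation, disclosure | Not stated |
| SAP, Timing of outcome assessments | both arms, baseline and week 6 | Not stated |

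One section puts baseline after allocation, one can be read the other way, and none settles the matter.

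**2. The plan's target, checked.** Inputs from the SAP's Sample size section: standardised effect 0.49, equal to 1.2 NRS points; alpha 0.05 (taken as two-sided); power 75%; 60 per group.

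- n per group = 2(1.960 + 0.674)²/0.49² = 58 (59 by the t-test), against 60 stated.
- Power at 60 per group = 76.5% (75.9% by the t-test), against 75% stated.
- Implied SD = 1.2/0.49 = 2.45 NRS points.

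The design figures reproduce, and the timing question does not change them.

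**3. Bias formulas.** Suppose knowing the arm makes reported baseline differ between arms by s (intervention minus control), while week-6 scores are unaffected. Let β be the slope of week-6 score on baseline.

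- Change score: bias = 0 − s, so size s.
- ANCOVA: bias = 0 − β·s, so size β·s. Using the change score as the ANCOVA outcome gives the same arm coefficient.

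A higher reported baseline in the intervention arm exaggerates benefit; a lower one hides it.

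**4. Numbers.** Both s and β are assumptions; β is set at 0.5.

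| s | Change score, share of 1.2 | ANCOVA, share of 1.2 |
|---|---|---|
| 0 | 0 | 0 |
| 0.25 | 0.25 (21%) | 0.5 × 0.25 = 0.125 (10%) |
| 0.5 | 0.50 (42%) | 0.5 × 0.5 = 0.25 (21%) |

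At s = 0.5, slopes of 0.3 to 0.7 give an ANCOVA bias of 0.15 to 0.35 points.

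**5. False-positive rate.** This was simulated with no true effect, 60 per arm, SD 2.45, baseline/follow-up correlation 0.5 and 3,000 runs per setting. The change score was compared by a test of means, standing in for Mann-Whitney.

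- s = 0.25: 8.5% for the change score and 5.7% for ANCOVA.
- s = 0.5: 20% and 10%. Over correlations of 0.3 to 0.7 the ranges are 16–30% and 7–19%.

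**6. Price of the unadjusted check.** A week-6 comparison without baseline has a standard error 1/√(1 − 0.5²) = 1.15 times that of ANCOVA at correlation 0.5. At 60 per arm, power is 76.5% against 87.3%. With the 105 completers split evenly, unadjusted power is about 70–71%.

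**The case against.** The strongest reply is that Study Regimen is loosely written, is arranged by arm rather than strictly by time, and should give way to Recruitment, where randomisation comes last. This stands to the extent that the actual order is unknown. It does not close the point, because the assessment in Recruitment may concern suitability only.

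A reader might infer more than the text supports in several ways:

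- *That baseline is not a pre-treatment measure.* The clinic session comes before the link, and treatment starts at log-in. Only the online questionnaire follows log-in, and the SAP does not name it as the analysis baseline.
- *That controls have no data for several comparisons.* The arm lists share NRS, QST, WOMAC, MSK-HQ, PSQI, 30CST, TUG, urine and blood, and both arms get actigraphy. Study Regimen's general visit list includes strength without distinguishing arms. The SAP says all outcomes were collected in both arms at both times. The gap lies in the protocol's text and is not established as conduct.
- *That NRS is not repeated in controls.* The synopsis and the SAP name NRS pain as primary, and the SAP measures it at follow-up. The protocol's Primary Objective is what disagrees.
- *That every outcome is exposed.* Ultrasound and actigraphy are not self-reports, and examiners are blinded. The credible route is through participant-reported or effort-dependent measures.

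It is also fair to say that the shift is assumed, may be zero, and has no known direction, and that reordering visits cannot alter data already collected.

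**Conclusion.** The documents conflict on whether baseline outcomes precede allocation, and none states that they do. Followed as written, Study Regimen yields baselines that are pre-treatment but given with the arm known, and the primary analysis depends on them.

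The possible bias is s for an unadjusted change score and β·s for ANCOVA. With s between 0 and 0.5 and a slope of 0.5, that is 0 to 0.5 and 0 to 0.25 NRS points against a target of 1.2. These values rest on assumptions about s and the slope, and on week-6 scores being unaffected by the same mechanism. They show what could happen and do not estimate what did. The larger figure applies only if the Mann-Whitney fallback is used.

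The difference in batteries concerns two secondary measures, leaves the primary outcome untouched, and is contradicted by the SAP. It needs reconciling, but no missing control data can be inferred from it.

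**What to change.** **Documents.** Reconcile the protocol's Primary Objective, Recruitment, Maintenance of Randomisation Codes and Study Regimen with the SAP's Randomisation and Timing of outcome assessments. Use one sequence: consent, eligibility, one full baseline battery for everyone, randomisation and disclosure, then the login link. Specify the same battery at week 6 in both arms, and state NRS pain as the primary objective throughout. Say that the clinic NRS, not the questionnaire completed after log-in, is the analysis baseline. Where actual conduct differed from this sequence, report what was done.

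**Data already collected.** The SAP records that the trial stopped on 19 March 2020 with 105 participants completing both visits, so the remedy lies in records and analysis:

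1. Compare each randomisation time stamp with the assessment date, and with the time if recorded. Report by arm how many baselines followed disclosure. Same-day cases without a clock time should be counted as unresolved.
2. Report by arm which participants have ultrasound and strength data at each visit.
3. Add to the SAP, before groups are compared, a sensitivity comparison of week-6 NRS without baseline adjustment. A shifted baseline cannot bias it, although it does not address unmasked reporting at week 6 itself.

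**Cost.** Wording changes, a records check and one extra analysis. The downside is the lower precision of the unadjusted comparison, so ANCOVA can stay primary if the records show that baseline came first.
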